#### Randomization

Patients, who meet all inclusion criteria and who do not fall under any exclusion criterion, are consecutively enrolled and randomly assigned at a 1:1 ratio to receive febuxostat or placebo through the dynamic allocation method using the following six background factors according to the minimization method: study site, gender, age (<65 or ≥65 years), SUA concentration (<8.0 mg/dL or ≥8.0 mg/dL), qualitative proteinuria (present or absent), and complication by diabetes (present or absent).

#### Endpoints

The primary endpoint of the FEATHER study is eGFR slope (change in eGFR per year, mL/min/1.73 m^2^/year) during the 108-week study period. The eGFR is calculated with the following equation defined by the Japanese Society of Nephrology: eGFRcreat (mL/min/1.73 m^2^) = 194 × [serum creatinine (mg/dLs) measured by the enzyme method]^-1.094^ × age^-0.287^ (× 0.739 if the patient is female).

The secondary endpoints are as follows: (1) the amount (mL/min/1.73 m^2^) and rate (%) of change in eGFR from baseline to weeks 24, 48, 72, and 108; (2) the amount (mg/dL) and the rate (%) of change in SUA concentration from baseline to week 108; (3) the proportion of patients whose SUA concentration became ≤6.0 mg/dL; (4) the incidence of renal deterioration defined by the commencement of dialysis or doubled serum creatinine concentration; (5) changes in biomarkers for renal function (serum cystatin C), oxidative stress (urinary 8-hydroxydeoxyguanosine and urinary L-type fatty acid-binding protein), and inflammation (serum C-reactive protein), as well as in variables for cardiovascular events (12-lead electrocardiogram, serum N-terminal pro-brain natriuretic protein, and albumin urine/creatinine ratio) to monitor the outcomes of ULT from baseline to week 108; (6) incidence of gouty arthritis; and (7) incidence of adverse events (AEs).

For safety assessment, AEs should be evaluated on clinical examination and in laboratory tests. The enrolled patient should visit the institution once every 4 weeks during the first 3 months and once every 3 months thereafter (Table 2). The investigator should evaluate patient compliance through history taking at each visit.

**Table 2 T2:** Schedule for observation, testing, and assessment

		**Timing**													
**Items**		**Eligibility confirmation**	**Enrollment and assignment**	**Baseline**	**Treatment phase**										
Visit^a^		1		2	3	4	5	6	7	8	9	10	11	12	13
Week after treatment onset^a^		-4		0	4	8	12	24	36	48	60	72	84	96	108
Acquisition of informed consent		X													
Pregnancy test^b^, gender, and date of birth		X													
Smoking history, anamnesis, and complications				X											
Status of study drug intake					X	X	X	X	X	X	X	X	X	X	X
Status of concurrent therapy^c^		X		X	X	X	X	X	X	X	X	X	X	X	X
Commencement of dialysis					X	X	X	X	X	X	X	X	X	X	X
Development of gouty arthritis					X	X	X	X	X	X	X	X	X	X	X
Development of adverse events					X	X	X	X	X	X	X	X	X	X	X
Height (second visit only), body weight, and BMI				X						X					X
Blood pressure (systolic, diastolic) and pulse rate		X^d^		X	X	X	X	X	X	X	X	X	X	X	X
12-lead electrocardiogram				X^e^											X^f^
Hematology blood chemistry^g^, and urinalysis^h^		X^d^		X	X	X	X	X	X	X	X	X	X	X	X
Blood	Serum urate^i^ and creatinine concentrations	X^d^		√	√	√	√	√	√	√	√	√	√	√	√
	T-C, HDL-C, and TG			√ at fasting											
	HbA1c	X^j^		√						√					√
	Markers^k^			√						√					√
Urine	Urinary creatinine, albumin, and urate^i^ concentrations			√						√					√
	Markers^k^			√						√					√
Blood sampling volume for measurement at the central laboratory (mL)				16	10	10	10	10	10	16	10	10	10	10	16

X: Measurement at the institution’s laboratory; √: Measurement at the central laboratory.

^a^Corresponds to the time of completion, discontinuation, or withdrawal.

^b^For the premenopausal female patient only.

^c^Antihypertensives, antihyperlipidemics, antidiabetics, non-steroidal anti-inflammatory drugs, adrenocortical steroids, theophylline, colchicine, and part of contraindicated and restricted concurrent therapies.

^d^Blood pressure, serum urate concentration, serum creatinine concentration, alanine aminotransferase, and aspartate aminotransferase are required to confirm eligibility. Urine protein (qualitative) is required to adjust allocation.

^e^Data obtained within 6 months before consent acquisition should be acceptable, unless cardiovascular or other events have developed. Data within 3 months before and after study completion should be acceptable.

^f^Red blood cell count, white blood cell count, platelet count, hemoglobin, and hematocrit.

^g^Alanine aminotransferase, aspartate aminotransferase, γ-glutamyl transpeptidase, blood urea nitrogen, creatine kinase, and blood electrolytes (Na, K, and Cl).

^h^Urine protein, urine glucose, occult blood reaction, urine pH, and N-acetylglucosaminidase.

^i^Serum urate concentration and urinary urate concentration should be measured at the central laboratory only during the study period. Measurement results obtained at the central laboratory should be transmitted to the institutions, but serum urate concentration and urinary urate concentration should not.

^j^Should be measured for the patient who is suspected of having diabetes.

^k^Serum cystatin C, urinary 8-hydroxy-2’-deoxyguanosine, urinary liver-type fatty acid-binding protein, serum C-reactive protein, and serum N-terminal pro-brain-type natriuretic peptide.

BMI, body mass index; T-C, total cholesterol; HDLC, high-density lipoprotein cholesterol; TG, triglyceride.

### Statistical methods and sample size

The statistical analysis of the primary endpoint should be made to demonstrate the superiority of febuxostat to placebo. The linear regression line will be fitted to the longitudinal data of the eGFR for each patient. In patients with CKD stage 3, the intergroup difference in the eGFR slope should be compared between the febuxostat group and the control group according to Student’s t-test (analysis of variance), with the stratified adjustment of stages 3a and 3b. Subgroup analysis by stage 3a and 3b should be conducted to check the heterogeneity of the effect size.

Based on previous study results [11,19], we calculated a sample size of 89 patients to detect a difference of 2.7 mL/min/1.73 m^2^/year in eGFR slope between the study groups at each CKD stage (3a or 3b), with a standard deviation of 7.2, a power of 80%, and a one-sided significance level of 0.05. This sample size will provide 94.2% power at a two-sided significance level of 0.05 to perform intergroup comparisons in the overall cohort of patients with CKD stage 3 (178 patients per study group; 356 patients in total). Assuming a withdrawal rate of 11%, the target number of patients is 100 in the subgroups of patients with CKD 3a and 3b, respectively, leading to 200 patients required for the study groups, respectively, and to a total of 400 patients with CKD stage 3.

Efficacy analysis should be performed on an intention-to-treat principle basis. All patients, who took at least one dose of the study drug and who have at least one measurement of the eGFR after study drug administration, should be included in the efficacy analysis set. All patients who took at least one dose of the study drug should be included in the safety analysis set. The interim analysis is not planned in this study. The data to be collected in the present study will be managed and analyzed by the following organization that is completely independent from the present study’s organizations: Non-Profit Organization Japan Clinical Research Support Unit.

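### The primary slope comparison leaves out all six minimisation factors; to the extent that they predict eGFR slope, its standard error is too large and its test conservative

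*Protocol article*

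**What the plan says.** The Randomization section assigns patients 1:1 "through the dynamic allocation method using the following six background factors according to the minimization method". The six factors are "study site, gender, age (<65 or ≥65 years), SUA concentration (<8.0 mg/dL or ≥8.0 mg/dL") and "qualitative proteinuria (present or absent), and complication by diabetes (present or absent"). CKD stage is not among them.

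The section on statistical methods and sample size fits a regression line to each patient's eGFR values. It then compares the slopes between groups by a t-test (analysis of variance) "with the stratified adjustment of stages 3a and 3b". Stage is the only covariate named, and no allocation factor appears in the stated primary model. The trial is sized "to detect a difference of 2.7 mL/min/1.73 m^2^/year in eGFR slope between the study groups at each CKD stage" and a subgroup analysis by stage is planned, which explains why stage is in the model.

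**The concern.** Minimisation forces the groups to be alike on the chosen factors. If a factor predicts eGFR slope, this balance makes the treatment difference vary less from one possible allocation to another. An analysis that omits the factor leaves its contribution in the residual variance and computes the standard error as if allocation had been simple. The estimate is not biased by the omission, but its reported uncertainty is too large.

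The article gives some reason to expect that the factors are not pure noise. Its Background section links hyperuricemia to CKD progression and describes a sex difference in the SUA level at which renal risk rises. A footnote to Table 2 shows that urine protein was collected at eligibility specifically for allocation.

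At stake are the calibration of the confidence interval and a modest amount of power, not the validity of a positive result.

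**Working it through.** **Inputs from the statistical methods section.** Difference 2.7 mL/min/1.73 m²/year; SD 7.2; 178 evaluable patients per group (356 in total); two-sided 5% test; 11% withdrawal. From the Randomization section: 1:1 allocation, six factors.

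**Assumed input.** R2, the share of slope variance explained by the allocation factors. The document does not give it; 0 to 0.20 is shown, with 0.30 as a further case in the simulation. SD 7.2 is taken as the total SD.

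**1. The plan's own figures reproduce.**
- Per stage, one-sided 5%, 80% power: n = 2 × (1.645 + 0.842)² × (7.2/2.7)² ≈ 88 per group by the normal approximation. By the noncentral t, 88 gives 79.8% and 89 gives 80.2%, so 89 is right.
- Overall: SE = 7.2 × √(2/178) = 0.763 and 2.7/0.763 = 3.538. Power = Φ(3.538 − 1.960) = 94.3%, or 94.2% by the noncentral t.
- Withdrawal: 89/0.89 = 100, 178/0.89 = 200, 356/0.89 = 400.

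**2. Effect of omitting balanced factors.** With full balance and additive effects, the true SE is 0.763 × √(1 − R2), while the planned analysis reports about 0.763. Hence:
- true size of the planned test = 2 × [1 − Φ(1.96/√(1 − R2))]
- excess width of the confidence interval = 1/√(1 − R2) − 1
- power of the planned test = Φ[(3.538 − 1.960)/√(1 − R2)]
- power of the adjusted test = Φ[3.538/√(1 − R2) − 1.960]

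| R2 (assumed) | True size | CI excess | Power, planned | Power, adjusted |
|---|---|---|---|---|
| 0 | 5.0% | 0% | 94.3% | 94.3% |
| 0.05 | 4.4% | 2.6% | 94.7% | 95.3% |
| 0.10 | 3.9% | 5.4% | 95.2% | 96.2% |
| 0.20 | 2.8% | 11.8% | 96.1% | 97.7% |

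The planned half-width is 1.96 × 0.763 = 1.50. The calibrated half-width is 1.42 at R2 0.10 and 1.34 at R2 0.20.

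**3. Gain in patients.** For the planned test to match the adjusted power, 2.7/SE must rise from 3.538 to 3.538 + 1.960 × [1 − √(1 − R2)], and the sample size grows with the square of that ratio.
- R2 0.10: (3.638/3.538)² × 356 ≈ 377, about 21 more.
- R2 0.20: (3.745/3.538)² × 356 ≈ 399, about 43 more.

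**4. Simulation check.** Six-factor minimisation was simulated with 356 patients, 64 sites and 6,000 runs under no effect. The biased-coin probability of 0.8, the factor prevalences and a site share of 20% of R2 are assumptions. Both models include stage; the adjusted model adds the five non-site factors.

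| R2 | Rejection, stage only | Mean SE / actual SD, stage only | Rejection, adjusted | Mean SE, adjusted |
|---|---|---|---|---|
| 0 | 4.9% | 0.764 / 0.764 | 4.8% | 0.764 |
| 0.10 | 4.0% | 0.764 / 0.721 | 4.6% | 0.733 |
| 0.20 | 3.3% | 0.764 / 0.701 | 4.8% | 0.700 |
| 0.30 | 2.4% | 0.764 / 0.662 | 4.6% | 0.665 |

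The formulas assume perfect balance. The simulated allocation leaves some imbalance, so its sizes are slightly closer to 5%. Direction and order of magnitude agree.

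**The case against.** The strongest reply is that nothing invalid follows. A conservative test does not inflate type I error, the estimate is unbiased by the omission, and power is at or above the planned figure. All of that stands.

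The second reply is that the size is unknown. Slopes fitted patient by patient carry measurement noise, which limits what baseline factors can explain. At R2 0.02 the true size is 4.8% and the interval only 1.0% too wide; at R2 0 the issue vanishes. The article calls the factors background factors and does not say that they are prognostic for slope. This stands too, so the conclusion must stay conditional.

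Third, a condensed article may leave covariates to an analysis plan that is not shown. This carries less weight, because the article itself names both the primary test and its adjustment.

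Three stronger readings are tempting and are not supported:
- A reader might infer that adjusting for stage is wrong because stage was not an allocation factor. A prespecified baseline covariate need not be one, and the trial is sized and its subgroups defined by stage.
- A reader might compute 356/(1 − R2) − 356 = 40 or 89 patients lost at R2 0.10 or 0.20. That describes reported interval width only. Minimisation has already given the estimate much of this precision, so the gain in power is worth about half as much.
- A reader might ask for covariate-by-time terms. They have no place in the planned two-step analysis of fitted slopes.

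**Conclusion.** The point holds as a conditional matter of calibration and efficiency. The mismatch between allocation and primary model is explicit in the article, and its direction is certain: if the omitted factors predict slope, the test is conservative. Its size is not certain, because it depends entirely on an R2 that the document does not supply. Across the assumed 0 to 0.20, it runs from no effect to an interval about 12% too wide, with about 1 to 1.6 percentage points of power to be gained at R2 0.10 to 0.20. These figures further assume a total SD of 7.2, additive factor effects and near-complete balance.

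A reader might infer that the planned standard error is wrong in any event, or that a positive finding would be in doubt. Neither follows: with no predictive factors the analysis is correctly calibrated, and otherwise it errs on the cautious side. The change is worth making because it costs almost nothing.

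**What to change.** Keep the 3a/3b adjustment. Add gender, age group, SUA category, proteinuria and diabetes, in the categories used for allocation, as main effects in the ANOVA/ANCOVA of the per-patient slopes. Either fit site as a random effect or leave it out and say so: 400 patients over 64 sites is about 6 per site, too few for fixed site effects to be useful.

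Fix the model in writing before unblinding. This is still feasible under the article's own terms, since data analysts are blinded and no interim analysis is planned.

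The cost is one model statement and about 5 degrees of freedom, from 353 to 348 residual with 356 evaluable patients. No new data are needed, because minimisation required all five factors before allocation. Sample size and allocation are unaffected.

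### The primary eGFR-slope comparison adjusts only for CKD stage and leaves unused a central week-0 albumin/creatinine ratio: an optional precision gain of uncertain, probably modest size.

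*Protocol article*

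**What the plan says.** In the protocol article, Statistical methods and sample size, a straight line is fitted to each patient's eGFR values. The slopes are then "compared between the febuxostat group and the control group according to Student’s t-test (analysis of variance"), "with the stratified adjustment of stages 3a and 3b". No other term is named for the primary comparison. A subgroup analysis by stage 3a and 3b is also planned, to look at heterogeneity of effect.

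Three other places bear on the point:

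- **Table 2** has a row headed "Urinary creatinine, albumin, and urate", marked for the central laboratory at weeks 0, 48 and 108. A baseline UACR can therefore be derived.
- **Endpoints** lists the "albumin urine/creatinine ratio" among the secondary outcomes, as a change from baseline to week 108. No stated analysis uses its baseline value as a covariate.
- **Randomization** names "qualitative proteinuria (present or absent") as one of six minimisation factors. Footnote d of Table 2 says this qualitative urine protein result is needed to adjust the allocation.

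**The concern.** By minimising on proteinuria, the plan signals that it may matter for outcome. It also schedules a graded, centrally measured value of a closely related quantity before treatment starts. Neither measure enters the primary model. To the extent that baseline albuminuria predicts eGFR slope within stage, that share of the slope variance stays in the error term. The confidence interval is then wider than it need be, both overall and within stages 3a and 3b.

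The stage-level comparisons have the most to gain. They drove the sample size and were planned at only 80% power, one-sided. The Trial status section says recruitment has ended, so the analysis model is one of the few remaining ways to gain precision.

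**Working it through.** **Inputs from the document** (Statistical methods and sample size). The plan aims to "detect a difference of 2.7 mL/min/1.73 m^2^/year in eGFR slope", "with a standard deviation of 7.2, a power of 80%, and a one-sided significance level of 0.05". From this, "we calculated a sample size of 89 patients" per group per stage, hence 178 per group and 356 in total, with 94.2% power overall at two-sided 0.05.

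**Input assumed.** R² is the share of slope variance explained by log week-0 UACR beyond CKD stage. The documents give no figure. I use 0% to 15%, including 2% as an unfavourable case.

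**Step 1: reproduce the plan.** SE = SD × √(2/n per group), with power from the noncentral t distribution.

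- Overall: 7.2 × √(2/178) = 0.763, and power for 2.7 at two-sided 0.05 is 94.2%. This matches.
- Per stage: 7.2 × √(2/89) = 1.079, and power for 2.7 at one-sided 0.05 is 80.2%. It is 79.8% at 88 per group, so 89 is the smallest number that reaches 80%. This matches.

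The sample-size calculation is therefore sound, and it takes no credit for a covariate.

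**Step 2: add the covariate.** Residual SD = 7.2 × √(1 − R²), put back into the same formulas. The equivalent size of a trial without the covariate is 356/(1 − R²). The one lost degree of freedom is negligible.

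| Assumed R² | Residual SD | SE, 178 per group | 95% CI half-width (1.96 × SE) | Overall power, two-sided 0.05 | Per-stage power, one-sided 0.05 | Equivalent evaluable patients |
|---|---|---|---|---|---|---|
| 0% | 7.20 | 0.763 | 1.50 | 94.2% | 80.2% | 356 |
| 2% | 7.13 | 0.756 | 1.48 | 94.6% | 80.8% | 363 |
| 5% | 7.02 | 0.744 | 1.46 | 95.2% | 81.9% | 375 |
| 10% | 6.83 | 0.724 | 1.42 | 96.1% | 83.7% | 396 |
| 15% | 6.64 | 0.704 | 1.38 | 96.9% | 85.5% | 419 |

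**Step 3: a smaller true effect.** If the true difference were 2.0 rather than 2.7 (a second assumption), overall power would be 74.3% at R² 0%, then 76.5%, 78.7% and 80.9% at 5%, 10% and 15%.

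**Step 4: what could dilute R².** The efficacy set admits patients with a single post-dose eGFR. A patient with values only at weeks 0 and 4 has a slope error SD of √2 × s ÷ (4/52.18) ≈ 18.4 × s, where s is the SD of one measurement. Assume s of 2 to 3 mL/min/1.73 m², 1% such patients, and that the planned SD does not already include this noise. The added variance is then:

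- s = 2: 0.01 × (18.4 × 2)² ≈ 14
- s = 3: 0.01 × (18.4 × 3)² ≈ 31

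The planned variance is 7.2² = 51.8. Baseline UACR cannot explain the added noise, so an R² of 10% would shrink to 0.10 × 51.8/(51.8 + 14) ≈ 8% or 0.10 × 51.8/(51.8 + 31) ≈ 6%.

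**The case against.** The strongest reply is that nothing here is wrong. The stage-adjusted comparison is valid, the article condenses a fuller protocol, and covariate-adjusted analyses are often left to that protocol or the SAP. The benefit rests on an R² that the documents do not supply. Choosing minimisation factors shows what was thought worth balancing, not how strongly it predicts slope. At R² near zero there is no gain, and at 2% overall power moves by less than half a point. UACR is also only one candidate. Adjusting for the allocation factors, which already include dipstick proteinuria and diabetes, would be more conventional, and the gain from UACR beyond those factors is not estimated here.

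Most of this stands, and it limits the point to a suggestion. It does not remove it. The article does fix the primary model and its one adjustment term, so a change to that model is a fair comment on stated text. None of these arguments identifies a harm from adding a prespecified pre-treatment covariate.

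A reader might infer three stronger things that the documents do not support:

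- **That the planned test is biased or the trial underpowered.** Omitting the covariate costs efficiency only, and the stated power figures reproduce.
- **That a baseline UACR exists for every patient.** Table 2 shows that it is scheduled; some values may be missing.
- **That the gain is known to be material.** That depends wholly on the assumed R².

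**Conclusion.** The point holds as an optional improvement in precision. The primary comparison uses stage alone, while a central baseline UACR is scheduled and unused as a covariate.

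Over an assumed R² of 0% to 15%, the standard error falls by between nothing and about 8% (0.763 to 0.704). At the planned difference, overall power gains about 0 to 3 points and per-stage power about 0 to 5 points. The overall gain is small because planned power is already 94.2%. The gain counts for more in the stage-level estimates, in interval width, and if the true difference is below 2.7. Noisy slopes from short follow-up make the lower part of the range more plausible.

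These figures rest on the planned SD of 7.2, 178 evaluable patients per group, and the assumed R².

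**What to change.** Before unblinding, prespecify the primary comparison as an ANCOVA of eGFR slope on treatment, CKD stage (3a or 3b) and log-transformed week-0 central UACR. Use the same covariate in the 3a and 3b subgroup models. Fill missing week-0 UACR values by one fixed rule that does not depend on treatment, such as the overall mean of the log values, so that no patient is dropped. Report the stage-only comparison as a sensitivity analysis.

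The cost is about one sentence of analysis text, one model degree of freedom and the fill-in rule. No new samples, visits or patients are needed. The article states that data analysts are blinded and that no interim analysis is planned, so the change can be made credibly while the blind holds.

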### Patients

The FEATHER study will consecutively recruit, at 64 medical institutions in Japan, 400 Japanese patients with hyperuricemia who have never had gout and are complicated by CKD stage 3a or 3b, who are aged 20 years or older, and who have no gouty arthritis (Table 1).

**Table 1 T1:** Inclusion and exclusion criteria

**Inclusion criteria**	**Exclusion criteria**
1. Men and women	1. Uncontrolled diabetes mellitus; HbA_1c_: ≥8.0% (JDS) or ≥8.4% (NGSP)
2. Age ≥20 years at informed consent	2. Systolic blood pressure ≥160 mmHg or diastolic blood pressure ≥100 mmHg
3. Patients with hyperuricemia; serum uric acid: 7.1-10.0 mg/dL	3. ALT or AST: greater than twice the upper limit of institutional reference range
4. eGFR: 30–59 mL/min/1.73 m^2^ (CKD stages 3a and 3b)	4. Change in serum creatinine level by more than 50% within 12 weeks before the confirmation of eligibility
5. No history of gout	5. Acute renal disease, nephrotic syndrome, other serious disease, dialysis, or renal transplantation
6. Written informed consent for study enrollment obtained from the patient	6. Complication or history of malignant tumor (not excluded from the study when the malignant tumor is not treated within 5 years and if there is no recurrence)
	7. History of hypersensitivity to febuxostat
	8. Intake of any one or more of the following drugs at the confirmation of eligibility: mercaptopurine hydrate, azathioprine, vidarabine, and didanosine
	9. Intake of any one or more of the following urate-lowering drugs within 4 weeks before the confirmation of eligibility: allopurinol, benzbromarone, probenecid, bucolome, and febuxostat
	10. Initiation of intake, dose modification, or discontinuation of intake of any one or more of the following drugs within 4 weeks before the confirmation of eligibility: losartan, fenofibrate, thiazide diuretics, and loop diuretics
	11. Continuous intake of salicylic acid drugs, e.g., aspirin (the patient taking low-dose aspirin [≤324 mg/day] need not to be excluded from the study)
	12. Hormone replacement therapy with estrogens
	13. Pregnancy, nursing, or planed pregnancy during the study
	14. Enrollment in other clinical trials within 24 weeks before providing informed consent
	15. Ineligibility at the investigator’s discretion

CKD, chronic kidney disease; Hba1c, hemoglobin A1c; JDS, Japan Diabetes Society; NGSP, National Glycohemoglobin Standardization Program.

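### The primary slope comparison adjusts for baseline renal function only as stage 3a or 3b; using the scheduled week-0 central eGFR as a continuous covariate would gain a little precision

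*Protocol article*

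**What the plan says.** Under Statistical methods and sample size, the protocol article builds the primary endpoint patient by patient: "The linear regression line will be fitted to the longitudinal data of the eGFR for each patient". It then states the test: "In patients with CKD stage 3, the intergroup difference in the eGFR slope should be compared" by Student's t-test (analysis of variance) "with the stratified adjustment of stages 3a and 3b". No other covariate is named for this test. A subgroup analysis by stage is planned as well.

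Table 1 (Patients) ties the stages to the entry range in inclusion criterion 4, an eGFR of 30–59 labelled "CKD stages 3a and 3b".

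Table 2 shows two creatinine measurements before treatment effects can arise. The first is at week -4 in the institution's laboratory; footnote d says that "serum creatinine concentration, alanine aminotransferase, and aspartate aminotransferase are required to confirm eligibility". The second is at week 0, where the table marks serum creatinine as central and reserves a blood volume for "measurement at the central laboratory". All later creatinine values are central too.

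The efficacy set contains every patient with at least one dose and at least one eGFR after dosing. It sets no baseline eGFR range.

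**The concern.** Baseline eGFR is measured on a continuous scale for every patient, in the same laboratory as the outcome data, but the primary model uses renal function only as a two-level stage. The model then treats a patient just above the stage boundary like one near 60, and a patient just below it like one near 30. If the rate of decline depends on the level of eGFR, part of the variation in slopes that baseline could explain stays in the error term. The standard error of the treatment difference is then slightly larger than it needs to be. Only precision is at stake. Neither the type I error nor the lack of bias is in question.

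**Working it through.** **The plan's own figures.** The inputs from Statistical methods and sample size are a difference of 2.7, an SD of 7.2, 80% power at one-sided 0.05 per stage, two-sided 0.05 overall, and 11% withdrawal.

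- Per stage: n = 2 × (1.645 + 0.842)² × 7.2² / 2.7² = 88 per group by the normal approximation. With the noncentral t, 89 per group gives 80.2% power.
- Overall: 2.7 / (7.2 × √(2/178)) = 3.538, and Φ(3.538 − 1.960) = 94.3%. The noncentral t gives 94.2%.
- Withdrawal: 89 / 0.89 = 100 and 178 / 0.89 = 200 per group, so 400 in total.

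All the stated figures reproduce.

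**How much of baseline eGFR the stage carries.** The article does not print the 3a/3b boundary. I assume the conventional 45, the midpoint of 30–60. For eGFR spread evenly over 30–60, the total variance is 30²/12 = 75. The two halves have means 37.5 and 52.5, so the between-stage variance is 7.5² = 56.25. The share kept is r² = 56.25/75 = 0.75. For a normal distribution with mean 45 and SD 8, truncated to 30–60 (also an assumption), r² = 0.68.

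**Residual variance, continuous against two-level.** Let ρ be the correlation of baseline eGFR with slope. The document does not give it, so I show a range. If the relation is linear, the ratio of residual variances is (1 − ρ²) / (1 − ρ²r²). For example, at ρ = 0.3 with an even spread it is 0.91 / (1 − 0.09 × 0.75) = 0.91 / 0.9325 = 0.976.

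Power is Φ(2.7 / (SD × √(2/178)) − 1.960), with SD = 7.2 × √ratio. This takes 7.2 as the SD after stage adjustment.

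| ρ (assumed) | Variance removed, even spread | Variance removed, truncated normal | Power at 178 per group |
|---|---|---|---|
| 0 | 0% | 0% | 94.3% |
| 0.1 | 0.25% | 0.3% | 94.3% |
| 0.2 | 1.0% | 1.3% | 94.5% |
| 0.3 | 2.4% | 3.1% | 94.8–94.9% |
| 0.4 | 4.5% | 5.7% | 95.2–95.4% |
| 0.5 | 7.7% | 9.6% | 95.8–96.1% |

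For ρ of 0.1–0.3 the gain is about 0.3–3% of residual variance. The largest power gain in that range is 94.88 − 94.27 = 0.6 points. As patients, it is 400 × 0.0025 = 1 to 400 × 0.0305 = 12.

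If 7.2 is instead the SD before any adjustment, then at ρ = 0.3 the stage model gives 95.5–95.6% and the continuous model 96.0%, a gain of 0.4–0.5 points.

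This calculation takes stage and covariate from the same eGFR value. If stage comes from week -4 and the covariate from week 0, measurement noise in each would shift these figures somewhat.

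**The case against.** The strongest defence is that the 3a/3b adjustment is a coherent, prespecified choice. It matches the per-stage sample size and the planned subgroup analysis. A stratified comparison is valid under randomization whatever the measurement noise, the stated power does not depend on a finer covariate, and the gain rests on a correlation that the document does not supply. The week-0 value may also already be a point on each patient's regression line, so it need not go unused. All of this stands, and it is why the point is minor. It does not remove the small gain: being a point on the line is not the same as explaining differences between patients' slopes.

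A reader might infer something stronger: that some patients have no stratum because their week-0 central eGFR falls outside 30–59, that leaving them out breaks the intention-to-treat principle, and that power drops below the stated 94.2%. The document does not support this. Each step needs stage to be read from week 0, and no sentence says that it is. Table 1 attaches the stages to the entry criterion, "eGFR: 30–59 mL/min/1.73 m^2^ (CKD stages 3a and 3b"), so on that reading every eligible patient is in 3a or 3b. The power loss would also require those patients to be excluded, whereas the efficacy set excludes no one by baseline eGFR. Nor is it a flaw if a patient staged at eligibility falls on the other side of the boundary at week 0, since a stratum fixed before treatment need not match a later measurement.

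**Conclusion.** The point holds as a minor, optional efficiency improvement. The stated primary test is valid, and the sample size and power are correct as given. Coding baseline renal function in two levels forgoes about 0.3–3% of residual slope variance, or at most about 0.6 points of power, for baseline–slope correlations of 0.1–0.3. The gain is nil if the correlation is zero and larger above 0.3. The figures rest on four assumptions from outside the document: the correlation, a linear relation, a boundary at 45, and an even or truncated normal spread of eGFR over 30–60.

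**What to change.** In the primary analysis, use ANCOVA on the per-patient slope with treatment and week-0 central-laboratory eGFR as a continuous covariate. This can replace the 3a/3b factor or be added to it; adding it keeps the link to the per-stage design and uses one more degree of freedom. State that every patient in the efficacy set stays in the analysis whatever the week-0 value. Define the 3a/3b subgroups by the eligibility eGFR, so that each eligible patient belongs to exactly one.

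The cost is one or two sentences of analysis wording before unblinding, with no new data or visits. The small downside is the assumption of a linear covariate effect. If that assumption is wrong, some of the precision gain is lost, but randomization still protects the treatment comparison.
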